## Discussion

This study will determine whether a multifaceted intervention is able to improve rates of repeat FOBT for CRC screening compared to usual care. It is important to stress that “usual care” at EFHC is at a high standard, consisting of team-based care for promoting CRC screening, point-of-care alerts for clinicians, and performance measurement and feedback to providers. These efforts to improve CRC screening are probably far greater than those in most private practices and CHCs. Health services research studies sometimes have relatively weak “usual care” groups; although the care for the control group may be “typical” care, it is not consistent with what the literature has shown to be evidence-based best practice. Thus, it can be hard to determine whether a new intervention truly has a marginal value beyond what has already been shown to be beneficial. In contrast, the usual care group in this study includes multiple evidence-based strategies to improve preventive service delivery through point-of-care quality improvement methods.

This study will examine use of an EHR system for population-based disease management and outreach among vulnerable patients cared for in CHCs. Very few studies have examined the benefit of using EHR-based interventions in this setting. These data are important, as more CHCs are seeking to become patient-centered medical homes with good health information technology (HIT) infrastructure. In addition, our study design will allow us to separate the effects of low cost technology (automated reminders) followed by more costly efforts (telephone outreach by a CRC Screening Coordinator). This tiered outreach strategy could help clinics maximize efficiency and make decisions as to when it is helpful to use more resource intensive strategies.

Although the main goal of this study is to determine the comparative effectiveness of the intervention compared to usual care, we also want to see if it is possible to achieve the high rates of adherence to CRC screening with annual FOBT that are necessary to achieve measurable reductions in CRC mortality. Few studies have examined the rate of repeat FOBT testing [11,12,39], and to our knowledge none have been conducted in populations with a high prevalence of barriers to screening (e.g., low literacy, varied cultural norms, transportation difficulties). A study from the Department of Veterans’ Affairs found that only 42% of men received adequate screening (FOBTs in at least 4 out of 5 years) [12]. A study of managed care plan enrollees in Washington state found that only 44% completed repeat screening within 2 years [11]. The assumption that FOBT is an effective CRC screening strategy presumes it will be done at least biennially, and cost-effectiveness studies of CRC screening strategies have found that the results are sensitive to the rate of adherence [13]. Our study will provide critical information for providers and policymakers as they consider different strategies (i.e., FOBT, flexible sigmoidoscopy, colonoscopy) to increase CRC screening among vulnerable populations.

If effective, the study intervention will serve as a model for CHCs of how to improve rates of repeat FOBT among vulnerable populations. Our intervention relies on technology that is increasingly available and declining in cost, including EHR systems, automated phone and text messaging, and FITs for CRC screening. This approach was taken to try to ensure generalizability and allow us to rapidly disseminate the intervention through networks of CHCs.

Conversely, if the intervention is not effective or if rates are suboptimal despite the intervention, our findings will spur future research and policy analyses about alternative screening strategies to address disparities. Endoscopy is more sensitive than FOBT for CRC screening and needs to be conducted less often. However, the costs of endoscopy are higher and many CHCs have limited access to endoscopy. Although there are significant barriers to using endoscopy for CRC screening, previous studies have shown that nurses can be trained to do flexible sigmoidoscopy effectively and safely [40-43]. Endoscopy is an acceptable screening strategy among populations with CRC screening disparities [44-50]. A study of screening colonoscopy for patients in East Harlem (55% Hispanic, 33% African American) found that 66% of patients completed colonoscopy with the aid of a patient navigator [51]. In addition, other studies have found that many patients cared for in safety net settings would prefer endoscopy to FOBT [47,50,52]. Such screening alternatives may need increased scrutiny should our intervention fail to achieve high rates of annual screening.

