**Methods:**

In this RCT, patients who are due for repeat FOBT are identified in the electronic health record (EHR) and randomized to receive either usual care or a multifaceted intervention. The usual care group includes multiple point-of-care interventions (e.g., standing orders, EHR reminders), performance measurement, and financial incentives to improve CRC screening rates. The intervention augments usual care through mailed CRC screening test kits, low literacy patient education materials, automated phone and text message reminders, in-person follow up calls from a CRC Screening Coordinator, and communication of results to patients along with a reminder card highlighting when the patient is next due for screening. The primary outcome is completion of FOBT within 6 months of becoming due.

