This paper describes the design of a comparative effectiveness study of an intervention to maximize the number of poor, predominantly Latino patients cared for at a CHC who complete a repeat FOBT within six months of becoming due for CRC screening. We first describe the CHC’s efforts to improve CRC screening rates prior to the start of this study. We then review critical aspects of the study design and intervention, including a) the use of an IRB-approved waiver of informed consent to randomize all eligible patients and achieve a fully representative study population, b) the conceptual framework for the multifaceted intervention, c) the outreach tools developed for each component of the intervention, d) separation of the intervention into two discrete phases to allow assessment of the marginal benefit of outreach by a CRC Screening Coordinator compared to lower-cost outreach strategies, e) the patient educational tools developed to provide feedback to patients with negative FOBTs and to improve successful completion of diagnostic colonoscopy among patients with positive FOBTs, and f) the outcome assessment. Finally, we discuss the significance of the study and some of the potential implications.

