### Conceptual framework

Most quality of care problems are due to a combination of patient, provider, and system-level factors. Any one of these may be rate-limiting so that care remains suboptimal even if most other aspects of care are done well. For example, if the care team routinely recognizes when patients are due for CRC screening but the patient does not understand why s/he needs to be screened or the instructions are intimidating, the test may not be performed. For this study, we developed a conceptual framework of likely barriers to optimal care and then designed the multifaceted intervention to address each of these barriers (Table 2). We believe that the components of the intervention may each have small, incremental effects that are both additive and synergistic, although we will not be able to determine the incremental effects of all individual components (see analysis plan below).

**Table 2 T2:** Conceptual framework for the intervention components

**Barrier**	**Intervention component(s) to address barrier**
No clinical systems in place to identify patients who need repeat screening, unless they present for care	EHR query to identify patients due for repeat screening; outreach to patients (half randomized to intervention)
No personal systems in place for patients to track when preventive services are due	Automatic phone/text reminders to remind patients they are due for screening
Low adherence to repeat screening because of financial and/or logistical barriers	Mail FOBT kits to patients
Patients forget to return FOBT	Automatic phone/text reminders to patients who do not return FOBT within 2 weeks
Low priority and/or risk perception for CRC	Call from CRC Screening Coordinator at 3 months to patients who do not complete FOBT to explain need for screening
Change of phone number and/or address makes initial reminders unsuccessful	When CRC Screening Coordinator calls at 3 months, he can use updated information (i.e., from a recent visit)
Patients do not understand instructions	Mailed FOBT kits include plain language information, instructions, and direct phone number for CRC Screening Coordinator

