### Two-phase intervention

#### Initial intervention

We group patients into weekly cohorts based on the date of their eligible FOBT between March 2011 and March 2012. Every Monday, all patients due for repeat FOBT screening in the coming week have a FIT kit mailed to their home, along with a letter from their primary care provider and the FIT instructions. We then send the automated phone call and two days later a text message via the commercial system (CallPointe; Tuscon, AZ) that EFHC uses routinely for patient reminders and health promotion messages. The system software allows us to track the number of completed phone and text messages, and whether the phone message is answered by a person or a machine.

Two weeks after the initial reminders and FIT kit mailing, we query the EHR to identify patients who did not return the mailed kit. Those who do not return the kit receive another automated phone call and text message.

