#### Personal calls by CRC Screening Coordinator at three months

Three months after the initial outreach and FIT kit mailing, we again query the EHR to identify patients in the intervention group who have not completed screening; the CRC Screening Coordinator then attempts to contact them by phone. We chose this three month cutoff because in previous studies it took 3–4 months to see the full effect of an initial outreach intervention [14,21]. By waiting three months until we can see the full effect of the initial intervention, we should be able to estimate the incremental effectiveness of the CRC Screening Coordinator calls beyond the effects of the initial outreach. In addition, by waiting three months to make personal calls, we may be able to contact patients who have changed phones or addresses but who had a clinical encounter during this period and now have updated information in the EHR. If the CRC Screening Coordinator is able to speak with the patient, he explains why repeat testing is needed, answers questions, and explores barriers to completing the FIT. If the patient verbalizes willingness to complete the test, another FIT kit is mailed to them. Persuasion theory suggests that obtaining verbal commitment will increase the proportion of patients who will actually complete the test [22,23]. If the CRC Screening Coordinator only obtains voicemail, a standard script is read reviewing key points and leaving a direct telephone number for contact.

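### The Discussion credits the design with separating the effect of automated reminders, but the first tier is a mailed-kit package and the randomised design can estimate only that package

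*Protocol article*

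**What the plan says.** In its second paragraph, the Discussion says that "our study design will allow us to separate the effects of low cost technology (automated reminders) followed by more costly efforts", and goes on to offer this tiering to clinics as a guide to when more resource-intensive outreach is worthwhile.

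The rest of the article describes the design as follows.

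- **Arms.** The Abstract says patients are "randomized to receive either usual care or a multifaceted intervention". There is no third arm.
- **First tier, mailing.** Under Initial intervention, patients coming due "have a FIT kit mailed to their home, along with a letter from their primary care provider and the FIT instructions".
- **First tier, reminders.** For the same patients, the same section continues: "We then send the automated phone call and two days later a text message via the commercial system".
- **Two-week repeat.** "Those who do not return the kit receive another automated phone call and text message".
- **Second tier.** Three months after the mailing, "we again query the EHR to identify patients in the intervention group who have not completed screening", and the coordinator telephones those patients.
- **Purpose of the two phases.** The Background gives it as "to allow assessment of the marginal benefit of outreach by a CRC Screening Coordinator compared to lower-cost outreach strategies", where the cheaper tier is described in general terms.
- **Stated limit.** The Conceptual framework says "we will not be able to determine the incremental effects of all individual components".
- **Component analysis.** The Analytic plan has a logistic regression of FIT completion on the number and type of components actually received, described as an association.

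**The concern.** The Discussion names the first tier as automated reminders. The Initial intervention section shows a package in which the mailed kit, letter and instructions come first and the call and text follow. The article elsewhere treats these as distinct: Table 2 assigns the mailed kit to financial and logistical barriers, and the reminders to keeping track of due dates and to forgetting.

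What is at stake is how a first-tier result would be interpreted. If completion rises before any coordinator call, a reader relying on the Discussion could credit the calls and texts. A health center might then adopt these without mailing kits, a strategy that the trial never assigns to anyone. On the article's own framework, the kit addresses a barrier that a reminder does not.

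**Working it through.** The article gives no numerical result on this point, so there is no figure to reproduce. The check is whether the design, as assigned, can identify a reminder effect.

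**Step 1: arm sizes.** From Identification of eligible patients and randomization: 28 patients shared an address across 14 households, and 422 had a unique address. The total is 28 + 422 = 450. Seven households went to each arm. With 28 patients in 14 households of at least two, each household has two, so 7 × 2 = 14 patients per arm. Half of 422 is 211. That gives 14 + 211 = 225 per arm, assuming the 422 were split evenly.

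**Step 2: what is assigned in the first tier.**

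| Arm | Mailed kit, letter, instructions | Automated call and text | Patients |
|---|---|---|---|
| Usual care | not assigned | not assigned | about 225 |
| Intervention | assigned | assigned | about 225 |
| Reminders only | not assigned | assigned | 0 |
| Mailing only | assigned | not assigned | 0 |

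Intervention patients who repeat the test shortly before their due date receive no outreach, so they do not fill the last two rows. The two-week repeat goes to patients who have already been mailed a kit, so it does not fill them either.

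**Step 3: identifiability.** Write the expected completion rate as a + k × (mailing) + r × (reminders).

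- Usual care: a
- Intervention: a + k + r
- Difference between arms: k + r

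The design matrix has rows (1, 0, 0) and (1, 1, 1). Its rank is 2, against 3 parameters. Only a and the sum k + r are estimable. If the components act synergistically, as the Conceptual framework expects, an interaction term joins the sum and there is no unique share due to reminders.

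**Step 4: what the planned regression adds.** Receipt will vary: some kits will be returned to sender, and some calls and texts will not be completed. The regression on components received can use that variation, but the variation is not randomised.

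- Receipt depends on whether a patient can be reached, which may itself be related to completing the test.
- The second call and text go only to those who have not returned the kit, so receiving more reminders is partly a consequence of not having completed.

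The result is an association, as the Analytic plan says. It is not a separation provided by the design.

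**Step 5: which contrast would answer the tier question.** Before coordinator calls begin, the arms differ by the first-tier package. A comparison of both arms up to that point is randomised. The three-month EHR query is described for the intervention arm only, as a step to find whom to call, and the Analytic plan names no randomised contrast for the first tier.

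**The case against.** The strongest reply is that, in context, the sentence contrasts two successive tiers and does not claim a reminder effect apart from the kit. The Background speaks of lower-cost outreach strategies in the plural, the section on coordinator calls measures them against the initial outreach as a whole, and a later paragraph of the Discussion lists messaging and FITs side by side. All of this stands. It reduces the defect to a wrong name for the first tier, but the name still tells readers what the effect is an effect of.

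Four stronger readings are tempting, and the documents do not support them.

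- **That nothing at all can be learned about reminders.** The system tracks completed calls and texts, and a regression on components received is planned. It is weak evidence, but it exists.
- **That the Discussion flatly contradicts the Conceptual framework.** Being unable to assess every component is compatible with separating two tiers. That sentence is a disclosure of the limit.
- **That usual care receives none of the first-tier content.** The same FIT is stocked in all clinics and used in both groups, and the article does not say that the redesigned instructions were withheld from usual care. What the article describes for the intervention arm alone is the mailed and automated outreach.
- **That the absence of a three-month comparison is an error.** A condensed article may leave a secondary comparison to a fuller plan. It is offered below as an improvement only.

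It is also fair to say that a center would have to overlook the Abstract, Table 2 and the intervention section to adopt reminders without kits on this evidence. That keeps the consequence modest.

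**Conclusion.** The point holds as a mislabelled tier. The randomised design can estimate the effect of the first-tier package against usual care; it cannot isolate automated reminders, because no patient in either arm is assigned reminders without the mailed kit. The regression on components received does not change this, since it gives a non-randomised association affected by reachability and by the rule for the two-week repeat.

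No numerical bias can be attached to the point. Its size is one phrase in the Discussion and the interpretation of one secondary question. The primary intention-to-treat comparison at six months is unaffected, and the priority is minor. The conclusion rests on the intervention being assigned as the Initial intervention section describes.

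**What to change.** **Wording.** In the Discussion, name the first tier as the initial mailed-outreach package (FIT kit, provider letter, instructions, and automated call and text), and add that the design does not isolate the effect of the reminders. This matches the terms already used in the Background and in the section on coordinator calls.

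**Optional improvement.** Add to the Analytic plan a secondary intention-to-treat comparison of FOBT completion in both arms, from dated EHR results, up to three months from the scheduled weekly-cohort mailing date. Apply the same date rule to usual care; each patient's date follows from the qualifying FOBT, so it can be computed in both arms. Counting from the scheduled mailing rather than the due date matters because kits go out on the Monday for patients due in the coming week, and the coordinator's calls are timed from that mailing. The window then closes before any coordinator call. Patients tested shortly before their due date should be handled as in the main analysis.

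**Cost.** One sentence of text, one extra secondary analysis on dates needed for the primary outcome anyway, and giving up any claim about reminders as a stand-alone tool.
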